#### Effect evaluation data analysis plan

2.8.2

Background characteristics will be presented by means of descriptive statistics. Demographic characteristics (i.e., participants’ educational level, age, gender, ethnicity, organization and job tenure, duration reporting to manager, and department) will be used to determine the representativeness of the study sample and potentially to control for their impact on the effects (Bernerth and Aguinis, 2016).

We articulated the following directional hypotheses (H1 to H3) to evaluate the effectiveness of the intervention:

Hypothesis 1a (within-group): both Group 1 (dual-level) and Group 2 (employee-only) will show significant increases in need crafting behaviors from baseline to the 2-weeks and 1-month post-intervention follow-ups.

Hypothesis 1b (between-group): Group 1 will show significantly greater increases in need crafting behaviors compared to Group 2 at the 2-weeks and 1-month follow-ups.

Hypothesis 1c (sustainability): Group 1 will maintain higher levels of need crafting from the 2-weeks to the 1-month follow-up, while Group 2 may show some decline.

Hypothesis 2a (within-group): Group 1 will show significant increases in perceived need-supportive leadership behaviors from baseline to the 2-weeks and 1-month follow-ups, while Group 2 will show minimal or no change.

Hypothesis 2b (between-group): Group 1 will show significantly higher perceived need-supportive leadership behaviors compared to Group 2 at the 2-weeks and 1-month follow-ups.

Hypothesis 2c (sustainability): Group 1 will maintain elevated levels of perceived need-supportive leadership from the 2-weeks to the 1-month follow-up, while Group 2 will remain stable at baseline levels.

Hypothesis 3a (within-group): both groups will show increases in need satisfaction from baseline to the 2-weeks and 1-month follow-ups.

Hypothesis 3b (between-group): Group 1 will show significantly greater improvements in need satisfaction compared to Group 2 at the 2-weeks and 1-month follow-ups.

Hypothesis 3c (sustainability): Group 1 will maintain or further improve need satisfaction from the 2-weeks to the 1-month follow-up, while Group 2 effects may diminish over time.

Based on theoretical proximity to training content and previous research, the largest between-group differences were expected for perceived need-supportive leadership (the direct target of the leader intervention), followed by need satisfaction (downstream of both crafting and leader support), with more modest effects anticipated for need crafting behaviors (since both groups directly received crafting training).

In the intervention study, linear mixed-effects models (LMMs) will be used to evaluate the effects of interventions on need crafting behaviors, need satisfaction, and need-supportive leader behaviors (i.e., to test these hypotheses). LMMs are ideal for this design because they handle repeated measures (pre-test, post-test, and follow-up) and account for the nesting of participants within departments, addressing both individual and group-level variability. By modeling random effects for participants and departments, LMMs ensure that differences in responses over time and between groups are properly accounted for. Additionally, LMMs effectively manage missing data, allowing us to test interaction effects between time and group and providing a robust evaluation of intervention outcomes across multiple levels (e.g., Snijders and Bosker, 2012).

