### Study design

2.1

The current intervention protocol recommends a quasi-experimental mixed-methods design using a partially randomized delayed-start approach with three experimental groups. Departments (clusters) will be randomized to Group 1 (NC + NN) or Group 3 (delayed NC + NN); departments whose managers do not volunteer will form Group 2 (NC only, non-randomized). Group 2 will demonstrate the superiority of a multilevel intervention (i.e., its cumulative effects), whereas Group 3 will serve as a control group until its members have received the intervention.

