### Allocation to intervention

2.5

All departments that sign up will be treated as separate clusters, followed by randomization (e.g., using a random number generator) to assign each department to either Group 1 (immediate intervention) or Group 3 (delayed intervention). Participants without participating managers will automatically be assigned to Group 2.

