### Limitations

3.1

Several limitations of the proposed protocol should be emphasized. First, the design is quasi-experimental: although departments will be randomized to the immediate (Group 1) and delayed (Group 3) conditions, Group 2 will comprise departments whose managers do not volunteer and are therefore self-selected. Pre-existing differences between Group 2 and the randomized groups (e.g., in leadership quality or departmental climate) may confound between-group comparisons, as manager willingness to participate may in itself signal a more need-supportive environment. Second, the study will be conducted at a single site of one South African mining services organization and is restricted to white-collar employees, which constrains the generalizability of findings to blue-collar workers – for whom safety protocols structurally limit crafting opportunities – and to other industries, labor markets, and cultural contexts. Third, although the *a priori* power analysis indicates that 26–51 participants per group are required to detect large-to-medium effects, this calculation assumes independent observations; because participants are clustered within departments, non-trivial intraclass correlations will reduce the effective sample size and statistical power, and attrition across the six measurement waves may compound this. Because the planned linear mixed-effects models include department-level random effects, clustering is accounted for analytically rather than biasing estimates; the residual concern is statistical power, and the study may only be adequately powered to detect moderate-to-large effects. Fourth, because all groups will be drawn from a single organization, contamination is possible: employees and managers from different conditions interact daily and may share intervention content, diluting between-group differences.

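### None of the nine stated effectiveness hypotheses uses the randomized Group 1 versus Group 3 contrast; all rest on pre-post change or on comparison with the self-selected Group 2

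*Protocol article*

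**What the plan says.** **Allocation.** Section 2.1 states "Departments (clusters) will be randomized to Group 1 (NC + NN) or Group 3 (delayed NC + NN" and "departments whose managers do not volunteer will form Group 2 (NC only, non-randomized". Section 2.5 repeats the Group 2 rule: "Participants without participating managers will automatically be assigned to Group 2". The only randomized comparison is therefore Group 1 versus Group 3.

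**Roles.** Section 2.1 says "Group 3 will serve as a control group until its members have received the intervention". It also says "Group 2 will demonstrate the superiority of a multilevel intervention (i.e., its cumulative effects".

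**Hypotheses.** Section 2.8.2 introduces its list with "We articulated the following directional hypotheses (H1 to H3) to evaluate the effectiveness of the intervention" and sets out H1a to H3c, covering need crafting, perceived leader support and need satisfaction. H1b is typical of the between-group items: "Group 1 will show significantly greater increases in need crafting behaviors compared to Group 2". The mixed models in the same section are the means of testing these hypotheses.

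**Acknowledged weakness.** Section 3.1 concedes: "Pre-existing differences between Group 2 and the randomized groups (e.g., in leadership quality or departmental climate) may confound between-group comparisons". It adds that a manager's willingness to take part may itself be a sign of a more supportive environment.

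**The concern.** The design creates a randomized control and the hypotheses then leave it out. Change within a treated group mixes the intervention effect with retesting, demand effects and whatever else happens in the organization over those weeks. A Group 1 versus Group 2 difference mixes the effect of training managers with the difference between managers who volunteer and managers who do not.

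The second problem is sharpest for perceived leader support. H2b predicts a higher level in Group 1 at follow-up, not a greater increase, so a gap already present at baseline could satisfy it. Department random effects deal with clustering; they do not remove selection.

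The abstract's first question is whether the intervention improves outcomes over time. Group 1 against the still-untreated Group 3 addresses it on a randomized basis, yet no hypothesis asks it. A statistical analysis plan written to these hypotheses would inherit the gap.

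**Working it through.** **1. Groups named in each hypothesis (section 2.8.2).**

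| Hypotheses | Comparison | Uses Group 3? |
|---|---|---|
| H1a, H3a | Change from baseline within Groups 1 and 2, no comparator | No |
| H2a | Change in Group 1, set beside little or no change in Group 2 | No |
| H1b, H2b, H3b | Group 1 versus Group 2 | No |
| H1c, H2c, H3c | 2-week to 1-month course of Group 1 beside that of Group 2 | No |

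Group 3 appears in 0 of 9. The paragraph that follows ranks the expected between-group differences, again for two groups that both had crafting training, that is, Groups 1 and 2.

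**2. Could the contrast be run on the stated schedule?**

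- Section 2.7: all groups have a pre-test at T1, and Group 3 repeats the same battery at T3. The contents of the battery are not listed.
- Section 2.8.1: the outcome measure is completed on the training day before the workshop, and the three instruments are given at T2 to T4 (Groups 1 and 2) and T4 to T6 (Group 3).
- Section 2.9.1.1: the items listed for T1, and for Group 3 at T3, are nine process items (seven plus two).

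On the section 2.8.1 schedule, Group 3 has no outcome value at T3, when Group 1 has its 2-week post-test. At T4 a pre-workshop Group 3 value would exist, but with no earlier value to adjust for. On the section 2.7 schedule the contrast is possible if the battery contains the outcome scales. The sections have to be reconciled.

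**3. Illustration: pre-post tests.** The plan gives no size for non-specific change, so these inputs are assumptions, except n = 51 per group and alpha 0.05 (section 2.4). As a check on that n, a two-sample t-test at 80% power gives 50.15, so 51, for d = 0.50 one-sided. The plan's 26 for d = 0.80 is reproduced only two-sided (25.52). That mismatch is a separate matter, and nothing here depends on it.

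For a shift of d SD and baseline to follow-up correlation ρ, the standardized change is dz = d / √(2(1 − ρ)), and the paired t-test has non-centrality dz·√51. At ρ = 0.5, dz = d. Probability of two-sided significance with no intervention effect:

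| Shift (SD) | ρ = 0.3 | ρ = 0.5 | ρ = 0.7 |
|---|---|---|---|
| 0.2 | 0.22 | 0.29 | 0.44 |
| 0.3 | 0.43 | 0.56 | 0.77 |
| 0.4 | 0.66 | 0.80 | 0.95 |

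These are for one test at one time point, with independent observations.

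**4. Illustration: Group 1 versus Group 2.** With 51 per group, no true effect and an assumed selection bias b, the two-sample non-centrality is b·√(51/2). For b = 0.1, 0.2 and 0.3 SD this is 0.50, 1.01 and 1.51. The probability of two-sided significance is then 8%, 17% and 32%, against a nominal 5%.

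**The case against.** A reader might infer that the randomized contrast will never be analysed. The documents do not support that. Sections 2.7 and 2.8.1 speak of differences between the groups, section 2.8.2 allows time-by-group interactions, and section 2.10 asks whether changes differ between groups over time. A three-group mixed model could yield the contrast, and an unseen analysis plan may specify it. What stands is narrower: this wording names no Group 1 versus Group 3 contrast and no time point, whereas the nine hypotheses are written out and name other comparisons.

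A reader might also call Group 1 versus Group 3 the only unbiased comparison. It is the only randomized one. Sections 3 and 3.1 list contamination, dropout and lower motivation under delay, self-report and demand characteristics, all of which can affect it.

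Nor is every within-group hypothesis without a comparator. H2a has one in Group 2, although a self-selected one.

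Two further points are fair. The confounding of Group 2 is disclosed; but disclosure adds no randomized test, and it sits badly with the firm statement in section 2.1. And Group 1 versus Group 3 answers a different question: the full intervention against none. It cannot show what manager training adds to employee training, so the Group 1 versus Group 2 comparison keeps a purpose.

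**Conclusion.** The point holds as stated in the heading. By count, 0 of 9 effectiveness hypotheses use the randomized contrast, although section 2.1 gives Group 3 the role of control. Two are pre-post changes without a comparator, and the other seven involve Group 1 beside or against the self-selected Group 2. Followed as written, the plan rests its effectiveness claims on comparisons open to non-specific change or to confounding that it acknowledges itself.

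This conclusion is structural and needs no numerical assumption. The probabilities above show only how large the problem could be; they depend on assumed shifts, biases and correlations and ignore clustering by department.

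It should be settled before data collection. If Group 3's outcomes are not measured at T3, the concurrent control value for Group 1's 2-week post-test cannot be recovered later.

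**What to change.** 1. In section 2.8.2, add as the main effectiveness hypothesis for each outcome the baseline-adjusted Group 1 versus Group 3 difference before Group 3 is trained: at T3, and at T4 if Group 3 is measured before its workshop. Analyse departments as randomized, with department random effects. State that it estimates the full intervention against none.
2. Label the Group 1 versus Group 2 hypotheses as non-randomized and adjust them for the baseline outcome. Treat within-group changes as descriptive. In section 2.1, say that Group 2 will be used to explore the added value of the multilevel approach, not to prove it.
3. Reconcile sections 2.7, 2.8.1 and 2.9.1.1 so that the three outcome instruments are explicitly in the T1 battery for all groups and in Group 3's T3 battery.

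**Cost.** Changes to protocol and analysis wording, and a softer claim about dual-level superiority. If the T1 and T3 batteries do not already hold the outcome scales, 20 items (9 + 8 + 3) are added to existing survey waves. No new groups or waves are needed.

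### H2b compares leader-support levels at follow-up, not change, so a pre-existing gap from manager self-selection could confirm it without any NeedNurture effect

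*Protocol article*

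**What the plan says.** All of the hypotheses stand in the Protocol article, section 2.8.2 (Effect evaluation data analysis plan). The three between-group hypotheses are not worded alike:

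- H1b, need crafting: "Group 1 will show significantly greater increases in need crafting behaviors compared to Group 2 at the 2-weeks and 1-month follow-ups".
- H2b, perceived leader support: "Group 1 will show significantly higher perceived need-supportive leadership behaviors compared to Group 2 at the 2-weeks and 1-month follow-ups".
- H3b, need satisfaction: "Group 1 will show significantly greater improvements in need satisfaction compared to Group 2 at the 2-weeks and 1-month follow-ups".

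Two neighbouring hypotheses also concern leader support. H2a expects that "Group 1 will show significant increases in perceived need-supportive leadership behaviors from baseline to the 2-weeks and 1-month follow-ups". For the employee-only comparison it adds the clause "while Group 2 will show minimal or no change". H2c expects Group 1 to hold its gain, "while Group 2 will remain stable at baseline levels".

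Sections 2.1 and 2.5 randomize departments to Groups 1 and 3 only. Group 2 is formed from those without a participating manager. Section 3.1 lists this as a limitation, gives leadership quality as an example of a pre-existing difference, and adds that "manager willingness to participate may in itself signal a more need-supportive environment".

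Section 2.8.2 names linear mixed-effects models with random effects for participants and departments. It says these models permit tests of a time-by-group interaction, but does not say which contrast decides H2b. The only covariates mentioned are demographic, and their use is left open.

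**The concern.** H2b is the only between-group hypothesis stated on levels, and it falls on the outcome closest to how Group 2 is formed. If managers who volunteer already support their staff more, Group 1 starts higher on the scale that H2b tests, and H2b read literally is met by that head start.

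Perceived leader support is NeedNurture's direct target and, by section 2.8.2, the outcome where the largest between-group difference is expected. Section 2.1 gives Group 2 the job of showing that the two-level programme is superior. A confirmed H2b would be read as evidence for the manager training, although the test as worded cannot separate training from selection.

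**Working it through.** **1. Inputs.** From the article: alpha 0.05, 51 per group for d = 0.50 and 26 per group for d = 0.80 (section 2.4); directional hypotheses (2.8.2); department random effects (2.8.2). Not in the article, so assumed: a constant baseline gap g of 0.2, 0.3 or 0.5 SD in favour of Group 1; 4 to 8 departments per group; intraclass correlation (ICC) of 0.05 to 0.2; zero NeedNurture effect throughout.

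**2. The article's own figure.** With a two-sample t-test at 80% power, d = 0.50 needs 51 per group one-sided (64 two-sided). The stated 51 therefore reproduces as one-sided, which fits directional hypotheses and is the setting used below. The 26 for d = 0.80 reproduces only as two-sided (one-sided gives 21). That mismatch is a separate matter, and nothing here depends on it.

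**3. Level test, clustering ignored.** The noncentrality is g × √(n/2), with 2n − 2 degrees of freedom. For n = 51, √25.5 = 5.05 and the one-sided critical value is 1.660.

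| Gap (SD) | Noncentrality | P(H2b confirmed), n = 51 | n = 26 |
|---|---|---|---|
| 0.2 | 1.01 | 0.26 | 0.18 |
| 0.3 | 1.51 | 0.44 | 0.28 |
| 0.5 | 2.52 | 0.81 | 0.55 |

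Two-sided at n = 51, the figures are about 0.17, 0.32 and 0.71. If both follow-ups must be significant (simulation, one-sided, n = 51, within-person correlation 0.5 to 0.7), they are 0.12-0.16, 0.27-0.33 and 0.70-0.72.

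**4. Level test by department.** With k departments per group and m = 50/k people in each, a department mean has variance v = ICC + (1 − ICC)/m. The noncentrality is g/√(2v/k), with 2k − 2 degrees of freedom.

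- Lowest corner, k = 4, ICC = 0.2: v = 0.2 + 0.8/12.5 = 0.264. For g = 0.5 the noncentrality is 0.5/√0.132 = 1.38 against a critical value of 1.943, giving 0.34. For g = 0.2 and 0.3 the result is 0.12 and 0.18.
- Highest corner, k = 8, ICC = 0.05: v = 0.05 + 0.95/6.25 = 0.202. For g = 0.5 the noncentrality is 0.5/√0.0505 = 2.22 against 1.761, giving 0.68. For g = 0.2 and 0.3 the result is 0.21 and 0.35.

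**5. Change from baseline.** A constant gap cancels in the difference between follow-up and pre-training score. In simulation (gaps of 0 to 0.8 SD, 26 or 51 per group, no clustering), one-sided false confirmation stayed between 4.6% and 5.5% per time point.

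**6. Baseline as a covariate instead.** In non-randomized groups, adjusting for a baseline that correlates r with follow-up leaves a bias of g(1 − r). For g = 0.5 this is 0.25 SD at r = 0.5 and 0.15 SD at r = 0.7. Simulated false confirmation at 51 per group was about 41% and 27%. Covariate adjustment is therefore no substitute for the change contrast here.

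**The case against.** The strongest reply is that differential change is what the authors mean. Section 2.8.2 says the mixed models, with pre-test, post-test and follow-up, will test these hypotheses and allow time-by-group interactions. Section 2.10 asks whether changes differ between groups over time and names leader support. H2a and H2c both refer to baseline. On that reading H2b is loose wording, and an article may leave exact contrasts to a fuller plan. This makes the intended estimand plausible but does not assign the interaction to H2b. The same model can also deliver a group difference at each follow-up, which is what H2b describes. Random effects for departments do not absorb a fixed difference between groups. The point concerns what the text states, not something left out.

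The second reply is that section 3.1 discloses the confounding. It does, in general terms, but H2b leaves even the removable part in place.

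Three stronger readings are tempting and not supported:

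- A reader might infer that Group 1 is bound to start higher. The article says only that it may, and gives no size.
- A reader might infer that H2b is the trial's headline test. No hypothesis is designated primary, and section 2.7 calls need satisfaction the dependent variable.
- A reader might infer from H2a and H2c that a significant change in Group 1 beside a non-significant one in Group 2 will serve as the between-group comparison. The article never says so; they are labelled within-group and sustainability hypotheses.

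**Conclusion.** The point holds as a defect of wording with real consequences for inference. H2b, followed as written, can be met by a baseline difference alone, on the outcome most exposed to manager self-selection. How often this would happen depends on a gap the article does not give. For assumed gaps of 0.2, 0.3 and 0.5 SD at one follow-up, one-sided, the range is 0.26, 0.44 and 0.81 with independent observations. It is about 0.12-0.21, 0.18-0.35 and 0.34-0.68 at department level. The second set is closer to the planned model, so 0.81 should not be quoted as the error rate of this trial. Every value exceeds the nominal 0.05, and with no gap the level test keeps its nominal rate.

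The clauses in H2a and H2c about Group 2 not changing are a minor companion: a non-significant result does not establish stability.

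**What to change.** Reword H2b on change, to match H1b and H3b: Group 1 will show significantly greater increases than Group 2 in perceived need-supportive leadership from the pre-training score to 2 weeks and to 1 month.

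Name its test: the group-by-time contrast in the planned mixed model at each follow-up, taken as change from the pre-training TMIB-S score. Do not use the baseline score as a covariate in place of this contrast. Refer to the pre-training score rather than to T1, because section 2.8.1 places the first administration for Groups 1 and 2 on the training day, at T2.

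State beside it that the contrast removes only a constant baseline gap. Differential trends and regression to the mean arising from self-selection would remain.

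For H2a and H2c, report the change in Group 2 as an estimate with its confidence interval, and do not read non-significance as support for stability.

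The cost is wording only. The pre-training measurement and the model are already planned.

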### Process evaluation

2.9

It is important to note that the success of the intervention is not only dependent on its inherent qualities or characteristics. Instead, the success and subsequent outcomes of the intervention are also influenced by contextual factors (e.g., work environment and participant engagement) (Briñol et al., 2020). Consequently, process evaluation will be conducted throughout the study to determine contextual factors and their possible impact on the reach, effectiveness, adoption, implementation, and maintenance of the program of the intervention (De Angelis et al., 2020; Glasgow et al., 1999). Critical realism contends that the success of any intervention is more complex and dependent on the intricate interactions between causal mechanisms, which are different for the context of every intervention (Abildgaard et al., 2016). Critical realism does not exclude the value-add of the intervention itself. It states that these interactive mechanisms are indeed apparent in the intervention itself, but that the social, group, and organizational contexts in which the intervention is executed should not be disregarded (Spacey et al., 2019). Participants in an intervention may respond differently to the mechanisms and contexts to which they are exposed, leading to equally diverse interpretations of these. Considering the impact of factors that can constrain or enable the need-crafting intervention is vital, since the study will take place in an “open system.” Tied to the IGLO model, it will, thus, be essential to determine what factors may influence whom, why certain identified factors may have an influence, and what the potential impact of these may be on the outcomes of the study (De Angelis et al., 2020; Spacey et al., 2019). As a result, the effectiveness of the intervention will not be based solely on the content of the intervention itself, but also on the different experiences, perceptions, and interpretations of those who will participate in the intervention as well as the reasons they may respond as such (De Angelis et al., 2020; Roodbari et al., 2023).

As process evaluation will occur continuously throughout the entirety of the intervention study, fidelity measurement will be conducted through the process evaluation to determine the potential impact that various factors have on the study outcomes. Such factors include the delivery of the intervention, the degree of implementation of need crafting activities by participants, whether participants have been allowed to participate in need crafting, how useful participants have found need crafting, and whether they have, in fact, engaged with need crafting once back at their jobs (Randall et al., 2009; Spacey et al., 2019).

